### Preliminary analyses

3.1.

Our data and supporting documents will be submitted to the National Institute on Alcohol Abuse and Alcoholism’s National Data Archive (NDA) and will be available within three years of completion of the study. Groups will be compared for differences in demographics and pre-treatment alcohol use. Means and standard deviations will characterize continuous variables, and percentages and frequencies characterize categorical variables. We will assess the impact of sex as a biological variable. Our alpha threshold for statistical significance will be 0.05.

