### Treatment efficacy

3.2.

We will follow an intention-to-treat approach to provide unbiased group comparisons. Treatment efficacy will be assessed per our primary outcome, PEth-defined abstinence. In the Starting Phase, abstinence will be defined as a week-over-week decrease in PEth levels (yes/no). During the Sustaining Phase and Follow-up Phase, abstinence will be defined as PEth <20 ng/mL (yes/no). Separate generalized estimating equations (GEE) with logit link functions will be used to assess abstinence during treatment (11 assessments across 26 weeks) and follow-up (4 assessments across 52 weeks). The frequency of PEth-defined excessive drinking (≥200 ng/mL; yes/no) will also be analyzed with GEE. GEEs with appropriate link functions will also assess additional outcomes for the longest duration of PEth-defined abstinence, uEtG results (positive/negative), self-reported days of drinking, self-reported drinks per day, and alcohol-associated harms (cigarette smoking, drug use, utilization of costly medical care). All GEE models will include effects for groups, biological sex, time, and the group-by-time interaction. Statistically significant group-by-time interactions will be evaluated with Bonferroni corrected post hoc tests.

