### Power

3.5.

Our sample size (*n* = 200) is based on statistical power calculations with the primary outcome of detecting group differences in PEth-assessed alcohol abstinence across 11 assessments during treatment and 4 assessments in follow-up. Our missing data techniques will recapture some power lost due to attrition, but we take a conservative approach to ensure adequate power by basing power calculations on a sample size reduced by 25% (*n* = 150). Our pilot study found an increase in abstinence of 43% in the CM group compared to 0% in the Control group. Using methods previously described [45], this effect would result in >99% power with *n* = 150 when comparing abstinence among groups in treatment (G*Power software). While this effect is promising, CM meta-analyses and large RCTs consistently demonstrate odds ratios (ORs) as effect sizes ranging from 1.7 to 4.5 for increasing substance use abstinence [23,46–51]. In addition, CBT4CBT, which all participants will receive, has an effect size on substance use ranging from *d* = 0.11–0.37. These are modest and consistent with CBT interventions that are commonly paired with CM in past trials where CM demonstrated superiority to CBT [47,49,52]. Based on our pilot study, we expect an effect size no smaller than OR = 1.7, which accounts for the underlying effect of CBT in both groups. In the treatment and follow-up period, at a sample size of *n* = 150, we will have at least 80% power to detect a modest effect size of OR = 1.34.

For the secondary aim of reducing the frequency of PEth-defined excessive drinking, our group has consistently found secondary improvements in the odds of substance-related harms to be OR = 1.80 or larger. Assuming a sample size of n = 150, we estimate at least 80% power to detect an OR = 1.80 for reduction in PEth-defined excessive drinking during treatment or the follow-up period.

For analyses of the ANA, our proposed sample size of n = 150 will provide at least 80% power to identify an OR = 1.44 when there are as many as 10 predictors being modeled. This OR corresponds to a small but clinically meaningful change predicted by demographics, our ANA variables, and in-treatment PEth-defined abstinence.

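### Bonferroni after a significant group-by-time interaction is valid, but Holm's step-down controls the same 5% error and never rejects less; the gain is small and changing costs almost nothing

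*Protocol article*

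**What the plan says.** The Treatment efficacy section fits separate GEE models for abstinence "during treatment (11 assessments across 26 weeks) and follow-up (4 assessments across 52 weeks"). On model content it says: "All GEE models will include effects for groups, biological sex, time, and the group-by-time interaction". On multiplicity it says: "Statistically significant group-by-time interactions will be evaluated with Bonferroni corrected post hoc tests". The Preliminary analyses section sets the level: "Our alpha threshold for statistical significance will be 0.05".

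So the method is fixed, and it applies only once the interaction is significant. The article does not list the contrasts that make up the post hoc family, and it gives no reason for preferring single-step Bonferroni.

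**The concern.** With a group-by-time interaction in hand, visit-level comparisons are how the trial would describe when a contingency management (CM) effect appears and how long it lasts. The Discussion calls evidence for sustained effects after CM less conclusive and offers the 12-month follow-up as a response.

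Bonferroni holds every visit to the strictest threshold, however many other visits have already been declared different. Holm relaxes the threshold after each rejection without raising the family-wise error. A visit with a real difference can therefore be reported as non-significant under Bonferroni when an equally rigorous procedure would have declared it. The same rule covers every outcome modelled in that section.

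**Working it through.** **Inputs from the article.** Alpha is 0.05, taken as two-sided. There are 11 treatment and 4 follow-up assessments. Power rests on "basing power calculations on a sample size reduced by 25" per cent, so n = 150, or 75 per arm if allocation is 1:1. The literature is said to "consistently demonstrate odds ratios (ORs) as effect sizes ranging from 1.7 to 4.5". The article gives no power figure for the post hoc tests.

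**The plan's own figure.** The Power section cites "an increase in abstinence of 43% in the CM group compared to 0% in the Control group" and claims more than 99% power at n = 150. The pooled rate is 0.215. The null SE is √(2 × 0.215 × 0.785/75) = 0.0671 and the alternative SE is √(0.43 × 0.57/75) = 0.0572. Then (0.43 − 1.96 × 0.0671)/0.0572 ≈ 5.2, which is power above 99.99%. The figure reproduces.

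**Thresholds.** Bonferroni requires p ≤ 0.05/m at every visit. Holm requires the i-th smallest p ≤ 0.05/(m − i + 1) and stops at the first failure.

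| Family | Bonferroni | Holm, in order |
|---|---|---|
| 11 treatment visits | 0.0045 throughout | 0.0045, 0.0050, … 0.05 |
| 4 follow-up visits | 0.0125 throughout | 0.0125, 0.0167, 0.025, 0.05 |

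The first step is identical, so the chance of finding at least one visit is the same. Later steps are looser, so Holm never finds fewer.

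**Family-wise error.** This was simulated with 11 uncorrelated tests:

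| Visits with a true effect | Bonferroni | Holm |
|---|---|---|
| 0 | 0.049 | 0.049 |
| 5 | 0.027 | 0.048 |
| 10 | 0.005 | 0.050 |

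Holm uses the permitted 5%. Bonferroni leaves most of it unused once many effects are real.

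**Power with the interaction test applied first.** Assumptions, because the article does not state them: control abstinence 25%, correlation 0.5 between visits, time categorical, and a Wald interaction test at 0.05. A visit counts as found only if the interaction is significant and the visit passes its threshold.

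- *Treatment* (no effect at two of the 11 visits, rising to a peak at the other nine). At peak OR 3.5 the interaction is significant in over 95% of trials. The gain from Holm is about 3 to 6 points per visit for most onset shapes, with about 2 and about 7 as the extremes. Across peak ORs 2.5 to 4.5 it is about 2 to 6 points (about 1 to 4 at 2.5). At peak OR 1.7 it is under 1 point.
- *Follow-up, slow fade* (OR 3.5 falling to 2.45, that is, by 30%). The largest contrast in time is ln 3.5 − ln 2.45 = 0.357. Each visit's log-OR has SE of about 0.353. With correlation 0.5, the difference between two visits has SE √(0.353² + 0.353² − 2 × 0.5 × 0.353²) ≈ 0.353. The first-to-last change is therefore only about one standard error, and the 3-df interaction test is significant in about 13% of trials. Visits found overall are 8.2% with Bonferroni and 9.1% with Holm, a gain of about 1 point.
- *Follow-up, steeper fade from a large early effect.* The interaction is detected more often, and the gain is about 2 to 4 points.

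**The case against.** The strongest case against is that nothing here is wrong. Bonferroni is valid and conservative, these are secondary contrasts, and whether CM persists is answered first by the group effect in the follow-up model. Preferring a step-down method is a refinement that fits most plans using Bonferroni. All of that stands, and it is why the point is minor.

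The post hoc family is also inferred. The article names no contrasts and prints neither 0.0045 nor 0.0125. This limits the numbers but not the argument, because Holm rejects at least as much as Bonferroni in any family of two or more tests.

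Bonferroni also has one real advantage: it comes with simple matching simultaneous intervals, and Holm does not. The article does not call for such intervals, but the change is not wholly free of cost.

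A reader might infer a much larger loss by comparing the two methods in every simulated trial. For the slow-fade follow-up case this gives 70% against 79% per visit, and 38% against 60% for finding all four. The article does not support that reading, because it runs post hoc tests only after a significant interaction, which would be present in about 13% of such trials. Likewise, a gain from 61% to 73% per visit arises when the same OR of 3.0 holds at all 11 visits (control rate 20%). That is a model with no interaction on the logit scale, where the tests would run only on a 5% false positive. In slowly fading follow-up, what limits visit-level claims is the interaction test, not Bonferroni.

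**Conclusion.** The point holds as a cheap improvement, not as an error. Holm's advantage in testing is a mathematical fact: same family-wise error, no independence assumption, never fewer rejections. Its size here is small: a few points of per-visit power in treatment if effects are moderate to large, and close to nothing at the lower end of the article's own OR range or when follow-up effects fade slowly.

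These sizes rest on the assumed control rate, correlation, 1:1 allocation, categorical time and effect shapes, and on visit-by-visit contrasts. The direction does not. A reader should not infer that the primary comparison is underpowered or that the stated error control fails, since neither depends on this choice.

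**What to change.** In the Treatment efficacy section, replace Bonferroni by Holm step-down for the post hoc tests, with family-wise alpha 0.05 within each model's set of post hoc contrasts, and name that set (for example, the group comparison at each assessment). Report visit-specific odds ratios with 95% confidence intervals, labelled as unadjusted, beside the Holm-adjusted p-values.

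The cost is a few words, with no extra data or assumptions. The downside is that an unadjusted interval can exclude 1 while the Holm-adjusted p-value exceeds 0.05, so the report should say in advance that the adjusted p-values govern claims of significance.

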### Additional analyses

3.3.

#### ANA variables

3.3.1.

GEE with logit link functions for binary outcomes and identity link functions for continuously distributed outcomes will be used to investigate whether ANA variables collected at the enrollment visit are predictive of abstinence across follow-up. Further modeling will include in treatment PEth-defined abstinence and excessive drinking as potential predictors of abstinence in follow-up. For in treatment repeated variables (see Table 1), we will take the average of the repeated assessments as point-estimate predictors.

#### Economic analyses

3.3.2.

Economic analyses will examine resource use from the healthcare sector, state-policymaker, and societal perspectives [34–36]. The healthcare-sector perspective includes medical costs incurred by the system on behalf of participants, including the cost of interventions, and participant out-of-pocket costs. The state-policymaker perspective informs resource allocation decisions made in the interest of the public, who are responsible for funding healthcare for many individuals with AUD, as well as criminal-legal resources, and social safety-net programs. The societal perspective accounts for all resources utilized by, or on behalf of, individuals with AUD, including those mentioned above, and those more broadly associated with untreated or undertreated AUD and comorbid conditions, such as premature mortality, reduced labor productivity, and costs incurred by crime victims [34,37].

First, microcosting analyses will be conducted to identify resource use and estimate the costs associated with implementing and sustaining CM relative to the Control condition. Next, between-arm difference in predicted-mean costs will be calculated according to each stakeholder perspective over the intervention and follow-up periods. The resource costing method will be used to assign national real-world unit costs to each resource utilized. Then, between-arm differences in predicted-mean values for effectiveness measures, alcohol-free years and quality-adjusted life-years (QALY), will be calculated for each time period with generalized linear mixed-models to adjust for potential confounding factors. Finally, incremental cost-effectiveness ratios (ICERs) will be calculated for each perspective/effectiveness measure by time period, and cost-effectiveness acceptability curves estimated to assess the uncertainty surrounding each ICER.

### Missing data

3.4.

Missingness will be handled with maximum likelihood or multiple imputation and other sensitivity analyses, including “missing not at random” approaches [24,38–40]. Maximum likelihood and multiple imputation have both shown exceptional performance compared to other methods of handling missing data when the assumption of “missing at random” can be satisfied [40–44].

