If CM participants have an unexcused missed visit or do not ship their sample within a week of the study visit, the PEth sample will be considered positive. In such cases, reinforcers will be withheld, and the participant will return to the Starting Phase. The maximum CM reinforcer that can be earned per week of abstinence is $90 (e.g., for visits occurring once every 4 weeks the max is $360). The maximum total amount that can be earned for negative PEth results during the CM intervention is $1,820.

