#### Control group

2.3.3.

Participants will receive CBT4CBT with their reinforcers contingent on submitting blood samples, not PEth results. Blood sample collection will occur on a fixed schedule of once weekly (Weeks 1-4), then every other week (Weeks 6 and 8), followed by every four weeks (Weeks 12, 16, 20, and 24), and a last intervention visit occurring on Week 26 (see Fig. 1). Similar to previous studies, the amount of reinforcement allotted for each sample will be a base level of $20 or yoked to the CM group [23,24]. When Control participants submit a blood sample, they will receive a reinforcer amount that is equal to the average provided to CM participants during the previous month, resulting in earnings that approximate the CM group. For example, if the average earning per sample in the CM group was $50, Control participants will receive $50 for each sample submitted. Total Control group reinforcement could be as high as $1,820 but is expected to be 50% of that amount.

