#### Implementation measures

2.5.7.

The percentage of visits missed will serve as an indicator of attrition. Additionally, we will track the frequency of, and reason for, delayed PEth sample shipments. If a sample is shipped 1–7 days after the study visit, instead of the same say as the study visit, it will be coded as “late.” If a sample is not shipped within 7 days, it will be coded as missing, the reinforcers withheld, and reinforcers reset to $20 when the next PEth negative sample is received. To assess participant satisfaction for this study, we will administer CM participants the Client Satisfaction Questionnaire, in which an a priori mean score >23 will indicate overall satisfaction with our telehealth-based CM procedures [32].

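### The protocol prints two codes for an unshipped PEth sample without saying which enters the primary GEE, and offers maximum likelihood for a model that has no likelihood

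*Protocol article*

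**What the plan says.** Four parts of the protocol article bear on a PEth sample that does not arrive.

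- **CM group (2.3.2).** The rule opens "If CM participants have an unexcused missed visit" and continues, for those who "do not ship their sample within a week of the study visit, the PEth sample will be considered positive". The consequences follow: "In such cases, reinforcers will be withheld, and the participant will return to the Starting Phase".
- **Control group (2.3.3).** "Participants will receive CBT4CBT with their reinforcers contingent on submitting blood samples, not PEth results". No rule scores an absent Control sample as positive.
- **Implementation measures (2.5.7).** "If a sample is not shipped within 7 days, it will be coded as missing, the reinforcers withheld". No arm is named, although the reinforcer reset that follows fits the CM contingencies.
- **Treatment efficacy (3.2) and Missing data (3.4).** The primary outcome is to be analysed by intention to treat with "Separate generalized estimating equations (GEE) with logit link functions", one model for treatment and one for follow-up. For missing values, "Missingness will be handled with maximum likelihood or multiple imputation and other sensitivity analyses". The sensitivity analyses include missing-not-at-random approaches, and the two main methods are justified under missing at random.

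**The concern.** There are two separate problems.

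First, an unshipped CM sample has two printed codes, positive and missing, and the analytic plan does not say which is used. The positive code is written for one arm only. If it reached the primary data set, absent samples would count as drinking in CM and as unknown in Control, so the group contrast would carry a coding artefact.

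Second, one of the two named missing-data methods does not fit the named primary model. GEE solves estimating equations and specifies no full likelihood for the repeated outcomes. It therefore does not inherit the missing-at-random validity that the Missing data section claims for maximum likelihood. Taking that option leaves GEE on the available visits, which is generally valid only when missingness is unrelated to observed outcomes (or depends only on covariates in the model).

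What is at stake is the unbiased intention-to-treat comparison that Treatment efficacy promises.

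**Working it through.** **Planning figures.** The Power section reduces 200 by 25%: 200 × 0.75 = 150, as stated. Its power of over 99% for 43% v 0% also reproduces (75 per arm, two-sided 0.05, 1:1 allocation assumed). The 25% is a reduction in sample size, not a per-sample missing rate. It is borrowed below only as an illustrative missing fraction.

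**Step 1: the CM-only positive code, if it were used.** Let p be true abstinence in Control and OR the true odds ratio. Let m be the fraction of CM samples missing, taken as independent of outcome so that coding is the only distortion.

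- CM true rate: c = OR·p / (1 − p + OR·p)
- CM rate as coded: c(1 − m). Control is analysed on observed samples and stays at p.
- Apparent OR: [c(1 − m) / (1 − c(1 − m))] / [p / (1 − p)]

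No effect, p = 0.40 (assumed; the document gives no expected Control rate for this trial):

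- m = 0.25: 0.40 × 0.75 = 0.30; (0.30/0.70) / (0.40/0.60) = 0.64
- m = 0.10: 0.40 × 0.90 = 0.36; (0.36/0.64) / (0.40/0.60) = 0.84

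Other assumed Control rates, including the protocol's smallest expected effect, OR 1.7:

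| True OR | Missing | Rule | p = 20% | p = 30% | p = 43% |
|---|---|---|---|---|---|
| 1.0 | 25% | CM only | 0.71 | 0.68 | 0.63 |
| 1.7 | 10% | CM only | 1.47 | 1.43 | 1.36 |
| 1.7 | 25% | CM only | 1.15 | 1.08 | 0.97 |
| 1.0 | 25% | both arms | 1.00 | 1.00 | 1.00 |
| 1.7 | 25% | both arms | 1.63 | 1.59 | 1.53 |

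The distortion runs against CM and comes from the asymmetry. The same rule in both arms keeps a null at 1.0 and attenuates 1.7 only slightly.

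**Step 2: available-case GEE.** The check was a simulation with 6,000 participants, 11 visits, random-intercept logistic outcomes (SD 2) and permanent dropout depending on the previous result. There was one run per setting, so each fit is compared with the full-data fit of the same run. About 13–17% of samples were missing.

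| Dropout per visit | Full data | Independence | Exchangeable |
|---|---|---|---|
| Both arms 5% after a positive, 1% after a negative | 0.99; 1.85 | 0.98; 1.85 | 0.99; 1.84 |
| CM 5%/1%, Control constant 2.8% | 0.93; 1.83 | 1.01; 1.92 | 0.93; 1.81 |
| CM constant 2.8%, Control 5%/1% | 1.02; 1.89 | 0.95; 1.72 | 1.03; 1.89 |

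(The first value in each cell is the null setting, the second a positive effect.) Independence GEE drifts when the dropout mechanism differs by arm, in either direction. Exchangeable GEE stays within about 0.02, but these data were generated with a random intercept, which suits that structure.

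A harsher pattern (CM 12% after a positive and 2% after a negative, Control 4%) was run with 3,000 participants. Independence GEE gave 1.11 against 1.00 at intercept SD 1, and 1.20 against 0.97 at SD 2. That pattern loses about 54–56% of CM by visit 11, far beyond the planning figure. At 6%/2% in CM the estimates were 1.05 and 1.06.

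**The case against.** The strongest reply is that the sections have different jobs. The CM rule sits in the description of the intervention, and its stated consequences are withheld reinforcers and a change of phase. Implementation measures then codes the data, and the Missing data section handles what is missing. Control needs no positive rule because its payments do not depend on PEth results. On this reading nothing conflicts, and the OR of 0.64 describes an analysis that the analytic plan nowhere specifies. The reading is the natural one, and it stands as a reason not to call the primary contrast biased. It does not remove the need to say so: the two codes are in print for the same sample, and neither is tied to the primary outcome. Nor is phase wholly operational, because Treatment efficacy defines abstinence differently by phase.

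A reader might infer three stronger things that the document does not support.

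- **That missing CM samples are scored positive and then handled by maximum likelihood.** Both cannot apply to one sample; once it is coded positive, nothing is left to impute.
- **That the plan rests on maximum likelihood.** Multiple imputation is offered as the alternative, works with GEE, and is joined by missing-not-at-random sensitivity analyses. Maximum likelihood also fits the mixed models in the Economic analyses section.
- **That the plan expects attrition to differ by arm.** The Discussion says only that more visits might raise CM attrition or could lower it. Its drinking-related mechanism is lower attrition among those not reaching abstinence.

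The positive rule also covers only unexcused missed visits and late or unshipped samples, within the CM intervention. The follow-up model is not touched by it. Details of the imputation model and the working correlation may properly be left to an analysis plan that is not shown.

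**Conclusion.** The point holds in a limited form. The document gives conflicting codes for an unshipped CM sample and does not fix which one enters the primary GEE. It also names a missing-data method that the primary model cannot use.

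The coding bias is conditional on the CM rule entering the analysis, which the text does not establish. If it did, the bias would be against CM and could be large: a null becomes 0.64 with 25% missing and 0.84 with 10%, and at 25% missing the smallest expected OR of 1.7 falls to between 0.97 and 1.15. These figures rest on assumed abstinence rates, assumed missing fractions and missingness unrelated to outcome.

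The bias from an available-case GEE can go either way. It depends on how dropout differs by arm and on the working correlation, and it was small in many of the scenarios tried. The case for correction is that both ambiguities bear on the primary comparison and are cheap to remove.

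**What to change.** 1. State that the CM group rule on missed and unshipped samples governs reinforcement and phase only, and reconcile its wording with Implementation measures.
2. For the analysis, code missed or unshipped samples as missing in both arms.
3. Make multiple imputation the primary method, done separately by arm and using prior PEth, uEtG, self-reported drinking and enrollment PEth, followed by the planned GEE.
4. Remove maximum likelihood for outcomes analysed by GEE, or replace the GEE with a likelihood-based mixed logistic model. The second course changes the odds ratio from population-averaged to participant-specific, so the choice should be made explicitly.
5. Add missing counted as positive in both arms as a sensitivity analysis, alongside the planned missing-not-at-random analyses.

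The cost is plan wording and modest imputation programming, with no new data. It should be settled before outcomes are seen by arm.
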